#### Intervention

Our moderate exercise intervention will consist of a 12-week heartrate-controlled training program for a cycle trainer. Trainings will take place at the Radboud Sportcentrum in Nijmegen, at the UM Sports in Maastricht or in exceptional cases at a local sports facility of choice.

During the intervention, the subjects will be asked to follow the same diet as prior to study inclusion and are instructed not to participate in novel exercise regimes in addition to the training program that they were given.

The training program is personalized to heartrate reserve (HHR) and can be calculated in the following manner: HHR = HR_max_ minus HR_rest_, in which HR_max_ is the maximal heartrate measured during the VO_2_max test before intervention and HR_rest_ is the heartrate determined at rest. The program consists of 60 min of cycling for 2 times (week: 1–6) to 3 times (week: 7–12) per week. Each training will start with a warming-up of 5 min on 40% of the individual HHR, followed by a training intensity of 50 min on 50–65% of HRR and a cooling down of 5 min on 40% HRR. For convenience, heartrate zones according the HRR will be predetermined. During each training heartrate can be monitored continuously and recorded by a Polar chest band and results can be viewed on the subject’s personal Polar account.

Each week, the subject will be asked to send results of the trainings to the researcher so read out of heartrates can be evaluated to ensure adequate adherence to the training protocol. During weekly consultations by phone, the researcher will monitor compliance and motivate subjects to complete the intervention.

### Statistical analysis

Normality of data will be evaluated with Kolmogorov-Smirnov tests or visual inspection of histograms. Descriptive data will be expressed as mean ± standard deviation for parametric continuous variables or as median and interquartile range for non-parametric continuous parameters or percentage for categorical variables. To test individual effects of our exercise intervention, parameters of the immune, metabolic, or cardiovascular assessments respectively, will be compared before versus after intervention, for which data will be assessed by parametric paired T-tests or non-parametric Wilcoxon signed rank tests. Moreover, to test group effects of our exercise intervention, parameters of the respective systems will be compared between the intervention and the time control group, for which data will be compared by parametric T-tests or non-parametric Mann Whitney U tests. Since we assume that the different systems might influence each other in the occurrence of recurrent pregnancy loss, correlation analyses will be used to examine interrelationships, specifically correlating changes of NK cell phenotypes with metabolic and cardiovascular parameters. Correlations between immune, metabolic and cardiovascular data will be assessed by univariate and multivariate logistic regression analysisand calculated as crude and adjusted odds ratios to correct for possible confounders such as BMI. Statistical significance will be defined as *P* < 0.05 using SPSS version 28.0.

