The intervention consists of a personalized 12-week heartrate-controlled cycle training program, that must be carried out on top of a subjects regular exercise regime and diet. Heart rate will be monitored by a Polar H10 heartrate monitor chest strap during cycle trainings. If women don’t want to participate in the training intervention, they will be asked to participate in a timeline-control group in which they receive similar questionnaires and assessments of their immune, cardiovascular and metabolic system. However, instead of an additional cycle training program of 12-weeks, they only follow their regular exercise regime and diet during an identical period. In this latter group, women will be included under similar criteria as the intervention group, preferably in a 1:1 ratio. Comparability between groups will be assessed on baseline characteristics prior to the intervention.

For both the intervention and control group, women will be asked to additionally donate menstrual blood at 4 and 8 weeks during the 12-week interval in order to assess intra menstrual cycle variation of eNK cells. Subsequently, all women will receive an identical immune, cardiovascular and metabolic assessment after 12 weeks and 1 year after intervention, a short questionnaire for monitoring subsequent pregnancy outcomes. See Figure 1 for a schematic overview of study design.

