#### Primary objective

To determine the changes in CD56^bright^ eNK cell number, phenotype and function before and after a moderate aerobe exercise intervention in women with unexplained RPL.

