#### Secondary objectives

•To study baseline characteristics and baseline levels of physical activity in women with unexplained RPL.•To study immunological effects of an aerobe exercise intervention in women with unexplained RPL and compare these between endometrial and peripheral samples.•To compare immunological effects in women who undergo an aerobe exercise intervention and a timeline control group who do not follow an aerobe exercise intervention.•To evaluate additional effects of an aerobe exercise intervention on the vaginal microbiota (in relationship to eNK cell population) as it can influence the maternal immune system.•To evaluate additional effects of an aerobe exercise intervention on markers of cardiovascular and metabolic health that are known to be associated with adverse pregnancy outcomes in women with unexplained RPL.•To study additional effects of an aerobe exercise intervention on sympathetic nervous system activity, as the sympathetic autonomic system appears to be an important modulator of the immune system, the cardiovascular system, and the metabolic system.•To study additional effects of an aerobe exercise intervention on physical fitness levels measured by maximal oxygen consumption.•To monitor pregnancy outcome up to 1 year after an aerobe exercise intervention.•To investigate correlations between the immunological, cardiovascular and metabolic effects of an aerobe exercise intervention in women with unexplained RPL.

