### Study population and recruitment

Eligible women with two or more unexplained pregnancy losses, will be included during a visit at the RPL clinic at MUMC+ or first trimester pregnancy clinic at the RUMC. These women are mostly referred by their general practitioner or other regional clinics in the southern or eastern part of the Netherlands. A pregnancy prior to a pregnancy loss, must be confirmed at least by either serum or urine beta-human chorionic gonadotropin, as ectopic and molar pregnancies are excluded in this definition. According to current (inter)national guidelines, the clinical work-up of women with RPL includes; a standardized history from the couple, maternal screening for antiphospholipid antibodies (anticardiolipin, lupus anticoagulant and β2 glycoprotein I), maternal thyroid screening, assessment of anatomical uterine anomalies, paternal screening for sperm DNA fragmentation, and parental karyotyping if indicated (1). Only women with unexplained RPL, not aiming to conceive within the study time frame of 3 to 4 months are eligible to participate. Furthermore, to ensure that there is no influence of a recent pregnancy loss or birth, women should be at least 2–3 months after their last pregnancy loss or birth. Further exclusion criteria are age above 40 years, body mass index above 40, current use of immune suppressive medication or hormonal contraceptives, current infection with the human immunodeficiency virus or symptomatic genital infections such as chlamydia or gonorrhea, pre-existent diabetes mellitus, autoimmune disease or overt cardiovascular disease, and vaccination 1 month prior to or during sampling and intervention.

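### The primary objective rests on an uncontrolled before-after change labelled an exercise effect, while the comparison with the time-control group is only secondary and does not say what is compared

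*Protocol article*

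**What the plan says.** All references are to the protocol article.

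- **Primary objective.** It concerns the change in CD56bright "eNK cell number, phenotype and function before and after a moderate aerobe exercise intervention in women with unexplained RPL". No control group is mentioned.
- **Statistical analysis, before-after comparison.** "To test individual effects of our exercise intervention, parameters of the immune, metabolic, or cardiovascular assessments respectively, will be compared before versus after intervention". The methods named are the paired t-test and, where data are not normal, the Wilcoxon test.
- **Statistical analysis, group comparison.** The next sentence plans a second test, of group effects: "parameters of the respective systems will be compared between the intervention and the time control group", by t-test or Mann-Whitney U test. It does not say whether the parameters are T0-T3 changes or week-12 values, and it names no baseline adjustment for this test.
- **Secondary objectives.** The controlled contrast appears here: "To compare immunological effects in women who undergo an aerobe exercise intervention and a timeline control group who do not follow an aerobe exercise intervention".
- **Study objectives and design.** Of women who do not want to train it says: "they will be asked to participate in a timeline-control group in which they receive similar questionnaires and assessments". Both groups have the same 12-week assessment and give the same extra menstrual samples at weeks 4 and 8. A 1:1 ratio is a preference.
- **Study population and recruitment.** On entry, "women should be at least 2–3 months after their last pregnancy loss or birth". The stated purpose is to avoid any influence of a recent loss or birth. There are to be 30 trained women and at most 30 controls, with non-randomized allocation.

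**The concern.** A paired test in one arm estimates the effect of training plus anything else that moves the mean over the same 12 weeks. Two candidates matter here. One is time since the last loss: the entry rule shows that the investigators regard it as relevant, and a woman who enters at 2-3 months is about 5-6 months past the loss at T3. The other is drift in the flow cytometry measurements. Either could shift the mean with no exercise effect at all, and the analysis section would still call the shift an effect of the intervention.

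The study collects the data that would remove any such trend common to both groups, but the ranking of objectives puts the uncontrolled contrast first. Both tests are described as testing effects of the intervention. If the paired test is significant and the group comparison is not, the only ranking in the article favours the less informative one.

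**Working it through.** **1. The plan's own sample size.** Inputs from *Sample size*: difference 473, SD 600, alpha 0.05 (taken as two-sided), power 80%, two independent groups.

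n per group = 2 × (1.960 + 0.842)² × 600² / 473² = 25.3, rounded up to 26. The stated 25 is reproduced to within one woman. Power at 25 per group is 79.6% by the normal approximation and 78.0% by the noncentral t. Inflating 25 for 15% drop-out gives 25 / 0.85 = 29.4, so 30, as planned. This calculation is for a two-group comparison, not for the paired test that serves the primary objective.

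**2. Paired test under a trend with no exercise effect.** The documents give no trend, no SD of change and no before-after correlation, so the trend is an assumption, expressed in SDs of the within-woman change. The noncentrality is trend × √n. With n = 25 and 24 degrees of freedom the critical t is 2.064.

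| Assumed trend (SD of change) | Significant, n = 25 | Significant, n = 20 |
|---|---|---|
| 0 | 5% | 5% |
| 0.2 | 16% | 14% |
| 0.3 | 30% | 25% |
| 0.5 | 67% | 56% |
| 0.8 | 97% | 92% |

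(Around 20 and around 25 women for analysis are both mentioned, in *Sample size*.)

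**3. Between-group test of the changes, same settings.** If the trend is common to both groups it cancels. In simulation the rejection rate was 4.9% to 5.3% for trends of 0.2 to 0.8 SD.

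**4. If the trends differ between groups.** Self-selected groups need not share a trend. With 25 per group and noncentrality = difference × √(25/2), a difference in trend of 0.3 SD gives 18% significant results and 0.5 SD gives 41%. This compares with 30% and 67% for the paired test when the whole trend of that size falls on the trained group.

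**5. Price in precision.** Effect detectable with 80% power:
- paired, n = 25: 0.58 SD of change;
- between groups, 25 and 25: 0.81 SD of change;
- between groups, 25 and 15 (an assumed shortfall of controls): 0.94 SD of change.

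**6. What baseline adjustment recovers.** Take the plan's 473 and SD 600, 25 per group and an assumed before-after correlation ρ. The SD of change is 600√(2(1−ρ)) and the residual SD under ANCOVA is 600√(1−ρ²).

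| ρ | SD of change | Power, change scores | ANCOVA SD | Power, ANCOVA |
|---|---|---|---|---|
| 0.3 | 710 | 64% | 572 | 82% |
| 0.5 | 600 | 78% | 520 | 88% |
| 0.7 | 465 | 94% | 428 | 97% |

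The ANCOVA figures ignore the degrees of freedom spent on covariates and any baseline imbalance between the groups, so they are slightly optimistic. The 473 and 600 refer to a peripheral NK cell marker, not to eNK cells.

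**The case against.** **The control group is used.** A reader might infer from the before-after sentence that the controls are ignored. They are not: the next sentence plans the group test, and the sample size calculation is for two groups. This stands. The defect is one of rank and specification: the objectives put the uncontrolled contrast first, and the quantity compared between groups is left open.

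**Some sources of bias are weak.** Regression to the mean and cycle-to-cycle variation come readily to mind. Women are not selected on eNK values, so entry selection should not shift their mean. Random variation between cycles is noise that the paired test already allows for, and the week 4 and 8 samples are there to assess it. Season is partly averaged out: at about 4 women a month, 30 women take 7 to 8 months to enrol. The entry interval is meant to limit the influence of a recent loss, though drift beyond it remains possible. This stands as well, and the point rests on directional trends only.

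**The control group brings its own bias.** Controls are women who declined training, and allocation follows individual circumstances. This stands. The 5% error rate holds only if the trend is common to both groups, and adjustment for T0 alone does not remove selection.

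**The study is exploratory.** It describes itself so, and a rule for conflicting results may stand in an analysis plan that is not shown. This lowers the severity. It does not justify ranking the less informative contrast first when the controlled one is available, or calling an uncontrolled change an exercise effect.

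**Conclusion.** The point holds as a matter of priority and labelling. The primary objective depends on a before-after change in trained women that cannot be attributed to training alone, while the controlled contrast is secondary and incompletely defined. The 30% and 67% figures illustrate how sensitive the paired test is to a trend. They rest on assumed trends of 0.3 and 0.5 SD of change with 25 women, and nothing in the document supports a particular size.

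Two stronger readings are not supported. One is that a positive primary result would be false: the document shows no trend, only that the paired test could not exclude one. The other is that the group comparison would be unbiased: with non-randomized allocation it removes common trends and leaves confounding by selection. Since the study presents itself as exploratory, this should be fixed before analysis but does not undermine the study.

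**What to change.** - **Primary analysis.** Compare intervention and control on CD56bright eNK cells at T3 (or on the T0-T3 change) by ANCOVA. Adjust for the T0 value and for a short prespecified list of baseline covariates that the planned questionnaires and measurements supply, for example age, BMI, time since last loss and baseline activity. Reword the primary objective to match.
- **Within-arm change.** Report the paired T0-T3 change in each group as a descriptive estimate with a 95% CI, and do not call it an effect of exercise.
- **Interpretation.** State that allocation is non-randomized, so the contrast removes trends common to both groups but not selection bias, and limit causal wording accordingly.

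**Cost.** Only the wording of the objective and the analysis changes; no planned visit or sample is added. There are three real downsides. The detectable effect at 25 per group rises from about 0.58 to 0.81 SD of change before any gain from baseline adjustment. The number of controls is capped at 30 with no stated minimum, so 25 analysable controls are not assured. Residual confounding remains, and with groups this small the covariate list must stay short.

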On average, 30 new couples who experienced RPL visit our clinic every month, of which approximately 15 women have unexplained RPL. These women will be informed about the study by the health professionals in our clinic and a patient information folder will be handed out to women who are interested to read about the study in more detail. The health professional also asks for permission to pass their contact information to the study investigator. Within 1 week women will be contacted by the study investigator to get additional verbal information about the study and answer possible questions. During this consultation, the study investigator will ensure that all subjects will be given full and adequate verbal and written information about the nature, purpose, possible burdens and benefits of the study. Furthermore, it will be emphasized that participants are free to withdraw from the study at any time without specific reason. After eligibility is verified, women are free to take the time they need before deciding if they would like to participate or not. We estimate that monthly approximately 4 out of these 15 eligible women would like to participate in the intervention study. Additionally, we anticipate extra participants via RiNet (Reproductive Immunology network in the Netherlands)^1^ and via Freya (Dutch association for women with fertility problems).^2^ Information about the study and contact details will be provided on both websites. In this way, women who are interested in possible participation can contact the study investigator directly. Further course will be the same as for women who are informed about the study in the RPL clinic at MUMC+ or first trimester pregnancy clinic at the RUMC.

In our clinical experience we observed profound willingness in this specific patient group to participate in scientific studies which potentially help them and future patients. Our inclusion rate is however anticipated on the more modest side, because we do respect practical concerns, mainly related to time investment issues in couples who would like to conceive on short notice.

A total of 30 women with unexplained RPL will be included in this study to participate in the intervention group, additionally a maximum of 30 RPL women will be included under similar criteria in the timeline control group. Allocation was non-randomized as patients were allocated based on what was considered most appropriate for their individual circumstances.

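### The non-randomised intervention and control groups are compared with unadjusted two-sample tests of an unspecified quantity, so pre-existing differences can be read as exercise effects

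*Protocol article*

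**What the plan says.** Two sections of the protocol article describe how women enter the groups. Study objectives and design says: "If women don’t want to participate in the training intervention, they will be asked to participate in a timeline-control group". Study population and recruitment says: "Allocation was non-randomized as patients were allocated based on what was considered most appropriate for their individual circumstances". The first rests on the woman's own wish, the second on a judgement of what suits her. Neither is random.

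The intervention group is 30 women. For controls, "additionally a maximum of 30 RPL women will be included under similar criteria in the timeline control group", and the 1:1 ratio is only a preference.

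On imbalance, Study objectives and design says: "Comparability between groups will be assessed on baseline characteristics prior to the intervention". No consequence of that check is stated.

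The Statistical analysis section gives the purpose of the between-group comparison as "to test group effects of our exercise intervention" and states that "parameters of the respective systems will be compared between the intervention and the time control group". The tests are the T-test or the Mann-Whitney U test. Adjustment for confounders, with BMI as the example, appears only for the correlations between the immune, metabolic and cardiovascular data.

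The comparison with controls is listed under Secondary objectives. The primary objective is the before-after change in trained women, and the before-after comparisons use paired tests.

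**The concern.** Women who decline a 12-week training programme may differ from those who accept it in habitual activity, fitness, weight or available time. The recruitment section itself mentions time investment as a practical concern in couples who want to conceive soon. Such factors plausibly bear on the cardiovascular and metabolic measurements, and possibly on the immune ones. An unadjusted two-sample test cannot tell such a difference from an effect of training, yet the analysis section attributes the contrast to the intervention.

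The timeline-control group is the only part of the design that can separate training from time effects and regression to the mean. If the comparison with it is confounded, the study loses its main safeguard for interpreting the before-after result. The plan recognises confounding for the correlation analyses but leaves it unaddressed in the comparison most exposed to it.

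**Working it through.** **Group size.** The Sample size section gives a difference of 473, an SD of 600, alpha 0.05, beta 0.2, and 25 women per group (50 in total). Taking alpha as two-sided:

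n per group = 2 × [600 × (1.960 + 0.842) / 473]² = 25.26, which rounds up to 26 (52 in total).

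Power at 25 per group is 79.6% by the normal approximation and 78.0% by the exact t calculation. The plan's figure is reproduced to within two women in total and is not in dispute. I use 25 per group below.

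**Assumptions, because the documents give no figures.** The exercise effect is zero. The groups differ by d SD for reasons other than exercise. The baseline to week-12 correlation r is 0.5 to 0.7. Data are normal with equal variances, and tests are two-sided at 5%. The Mann-Whitney test was not simulated.

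**Week-12 values, difference fully persisting.** The noncentrality is d × √(25/2) = 3.536 × d, with 48 degrees of freedom.

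| d at week 12 | Noncentrality | Rejection rate |
|---|---|---|
| 0 | 0 | 5% |
| 0.2 | 0.71 | 11% |
| 0.3 | 1.06 | 18% |
| 0.5 | 1.77 | 41% |

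**Three analyses compared at d = 0.5 at baseline** (20,000 simulated trials per row). Stable means that the group difference is still d at week 12. Regressing means that it has shrunk to r × d.

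| Behaviour of the difference | r | Week-12 values | Change score | ANCOVA on baseline |
|---|---|---|---|---|
| Stable | 0.5 | 41% | 5% | 16% |
| Stable | 0.7 | 41% | 5% | 11% |
| Regressing | 0.5 | 14% | 14% | 5% |
| Regressing | 0.7 | 23% | 10% | 5% |

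**Why the ranking turns over.**
- Stable case: the change score has no bias, d − d = 0. ANCOVA subtracts only r × d and leaves d(1 − r), which is 0.25 SD at r = 0.5 and 0.15 SD at r = 0.7.
- Regressing case: ANCOVA has no bias, r × d − r × d = 0. The change score is biased by r × d − d = −d(1 − r), which is −0.25 SD and −0.15 SD, opposite in sign to the baseline difference.

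Age, BMI, activity score and centre were not modelled. The figures support use of the baseline value. The case for the other covariates rests on the selection mechanism, not on this simulation.

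**The case against.** Four points can be made for the plan.

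First, a reader might infer that only week-12 values will be compared and baseline discarded. The text does not say so. It speaks of parameters, the secondary objective speaks of comparing immunological effects, and the correlation analyses use changes. A two-sample test of changes fits equally well and holds about 5% when the difference is stable. This stands: the supportable defect is that the compared quantity is left open and confounders are not adjusted for. Even on the change reading, the test remains exposed to regression to the mean and to differing time trends.

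Second, nothing in the documents shows that the groups will differ, or by how much. This also stands. Differences can be read as exercise effects; it is not established that they will be. The 41% belongs to one assumed case, 0.5 SD fully persisting, under the week-12 reading.

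Third, the comparison is secondary, in a study that describes itself as explorative, and the paired primary test is untouched. This stands and lowers the weight of the point.

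Fourth, a fuller protocol or analysis plan may say what follows from the comparability check, and unwillingness to train may count among a woman's individual circumstances. The first part does not rescue the plan, because the article names the tests for this comparison and places adjustment elsewhere in the same paragraph. The second narrows the conflict between the two accounts of allocation, but who decides remains unclear.

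**Conclusion.** The point holds as a weakness that should be fixed in a secondary analysis. It does not invalidate the trial. The groups are formed non-randomly, the tests are unadjusted, the compared quantity is not fixed, and the contrast is attributed to exercise.

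The size depends on assumptions that the documents cannot settle. For a 0.5 SD baseline difference with r between 0.5 and 0.7, the false-positive rate of an unadjusted test runs from the nominal 5% (changes, stable difference) to 41% (week-12 values, stable difference). If the difference regresses, it is 14–23% for week-12 values and 10–14% for changes.

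A reader might also infer that ANCOVA is the clear remedy. It is not: it holds about 5% if the imbalance regresses but rejects in 11–16% if the imbalance is stable, where the change score holds 5%. Neither removes unmeasured confounding.

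**What to change.** In the Statistical analysis section, replace the unadjusted between-group tests with a linear model of the week-12 value on group. Adjust for the baseline value of the same parameter and a short prespecified covariate list, for example age, BMI, SQUASH score and centre. Transform skewed measures where needed. Report the adjusted difference with its 95% confidence interval.

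Present a covariate-adjusted change-score analysis alongside, and state in advance that agreement between the two strengthens the reading and disagreement limits it. Word the between-group result as an association.

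Reconcile Study objectives and design with Study population and recruitment on how women enter each group, including who decides.

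The cost is a revised analysis paragraph and no new data, since all these items are already collected. With 50 women, the example list leaves 50 − 7 = 43 residual degrees of freedom (intercept, group and five covariates), against 48 for the two-sample T-test. If the control group falls short of 1:1, fewer remain and the list should be shortened in advance.

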### Study procedures and data collection

In short, a questionnaire on baseline characteristics and on baseline exercise levels will be conducted before intervention. For immunological assessment, menstrual blood will be sampled before, during, and after intervention. Peripheral blood and a vaginal swab will be sampled before and after intervention. For assessment of the cardiovascular system, a transvaginal ultrasound examination of both uterine arteries will be performed before intervention. Hemodynamic responses during a tilt test and maximal oxygen consumption during a VO_2_max test will be measured both before and after intervention. For metabolic assessment, measurements of metabolic components in peripheral blood and urine plus body characteristics will be determined before and after intervention. The intervention consists of 12-weeks moderate training. One year after intervention women will receive a final short questionnaire regarding pregnancy outcome.

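### Read literally, the correlation analysis sets changes in NK phenotype against metabolic and cardiovascular values at an unnamed visit, whereas the objective is to correlate training effects in all three systems

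*Protocol article*

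**What the plan says.** The objective, last in the list under Secondary objectives, is to study "correlations between the immunological, cardiovascular and metabolic effects of an aerobe exercise intervention" in women with unexplained RPL.

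The Statistical analysis section describes the matching analysis as "specifically correlating changes of NK cell phenotypes with metabolic and cardiovascular parameters". Earlier in that section the same noun is used for the measured variables of all three systems: "parameters of the immune, metabolic, or cardiovascular assessments respectively, will be compared before versus after intervention". The sentence after the planned correlation gives the method: "Correlations between immune, metabolic and cardiovascular data will be assessed by univariate and multivariate logistic regression", reported as crude and adjusted odds ratios. Neither sentence names a visit for the metabolic and cardiovascular side or says that its changes are taken.

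Under Study procedures and data collection, the metabolic side is available twice: "measurements of metabolic components in peripheral blood and urine plus body characteristics will be determined before and after intervention". Tilt-test responses and maximal oxygen consumption "will be measured both before and after intervention". For the uterine arteries the same section says only that "a transvaginal ultrasound examination of both uterine arteries will be performed before intervention", while Study objectives and design has all women repeat an identical cardiovascular assessment after 12 weeks.

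**The concern.** Within a woman, an effect of training is her change from before to after. Whether effects in different systems go together is therefore a question about change against change. The analysis sentence attaches change to NK phenotype only. What follows is a set of variables at no stated visit.

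A level at one visit is a weak stand-in for the change in that variable. If the sentence were carried out literally, a real coupling of training responses could easily be missed. The direction reported could also depend on whether pre- or post-training values were picked, a choice the text leaves open until the data are in. The Introduction presents the interplay between systems as something no study has examined, so the analysis matters to the study's rationale even though it is secondary.

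**Working it through.** **The plan's own figures.** The article gives no expected correlation, power or sample size for this analysis. Its only computed sample size, under Sample size, is for a two-group comparison of an NK marker (difference 473, SD 600, alpha 0.05, beta 0.2). The normal formula gives 2 × (600 × (1.960 + 0.842) / 473)² = 25.3, so 26 per group against the stated 25. That is close enough, and it has no bearing on the correlation analysis. The number used below is the roughly 25 intervention-group women expected for analysis (30 × 0.85 = 25.5).

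**Assumptions not in the article:**
- r = 0.5 for the correlation between the observed changes.
- Pre-post correlation ρ of a metabolic or cardiovascular variable between 0.5 and 0.9.
- Equal SDs at the two visits.
- The NK change is related to the other variable only through that variable's change.
- Two-sided alpha 0.05.

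**Step 1: how a level relates to its own change.** Let Y0 and Y1 be the values before and after training, each with SD s.
- Cov(Y1 − Y0, Y1) = s²(1 − ρ), and SD(Y1 − Y0) = s√(2(1 − ρ)).
- Hence corr(Y1 − Y0, Y1) = +√((1 − ρ)/2).
- By symmetry, corr(Y1 − Y0, Y0) = −√((1 − ρ)/2).

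**Step 2: carry this to the NK change.** With a link only through the change, the correlation of NK change with a level is r × √((1 − ρ)/2), positive for the post-training level and negative for the pre-training level. At ρ = 0.8 this is 0.5 × 0.316 = 0.158. A simulation at these values gave +0.158 and −0.158, and 0.50 for change against change.

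**Step 3: power for a Pearson correlation by Fisher's z, n = 25.** For change against change, atanh(0.5) × √22 = 0.549 × 4.690 = 2.577. Then 2.577 − 1.960 = 0.617, which gives power 0.73. For change against level:

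| ρ | factor √((1 − ρ)/2) | shrinkage | absolute correlation | power |
|---|---|---|---|---|
| 0.5 | 0.50 | 2.0-fold | 0.25 | 22% |
| 0.7 | 0.39 | 2.6-fold | 0.19 | 15% |
| 0.8 | 0.32 | 3.2-fold | 0.16 | 12% |
| 0.9 | 0.22 | 4.5-fold | 0.11 | 8% |

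**Step 4: when the sign reverses.** Let k = SD after / SD before. The covariance of the change with the post-training level is proportional to k(k − ρ), which is positive when k > ρ. With the pre-training level it is proportional to ρk − 1, which is negative when k < 1/ρ. The two visits therefore give opposite signs only when k lies between ρ and 1/ρ: 0.5 to 2 at ρ = 0.5, 0.8 to 1.25 at ρ = 0.8, and 0.9 to 1.11 at ρ = 0.9. Outside that interval both visits give the same sign.

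**The case against.** The strongest reply is that the sentence need not mean levels. The word for the variables is generic and names what is measured, not a visit. The word for change can be read as governing both sides, and the stated objective supports that reading. On it, nothing shrinks and no sign flips. This stands as a reason not to call the plan wrong outright. It does not remove the ambiguity, because the literal grammar puts change on one side only and no other sentence corrects it.

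A reader might infer from the following sentence, which speaks only of data, that levels are definitely used. It does not show this: the same word covers the immune side, which is expressly a change.

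A reader might also infer a fixed loss of about threefold, or a sign that must reverse with the visit. The documents support neither. Threefold is the case of ρ near 0.8, and the reversal needs similar SDs. The article gives neither quantity, nor evidence that the link runs only through changes.

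The power figures are for a Pearson correlation, whereas the article announces logistic regression with odds ratios and names no binary outcome. They are therefore illustrative only and do not give the power of the analysis as planned. This objection stands in full, and it means the fix must deal with the method as well.

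Finally, a condensed article may leave visit and analysis set to a fuller document. That would answer a complaint about missing detail. Here the article states the analysis specifically, and what it states, read literally, does not match its own objective.

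**Conclusion.** The point holds as an unclear specification. Read literally, the analysis relates NK change to values at an unnamed visit and does not estimate the correlation of effects that the objective asks for. If it were carried out that way, dilution of about 2- to 4.5-fold is plausible. Where SDs are similar at the two visits, the direction would depend on the visit chosen. These sizes rest on the assumptions listed in the working and would differ if NK change also depended directly on a level. If the investigators intend changes on both sides, the loss is nil and only the wording needs repair. The primary objective is unaffected. This is a secondary analysis in a study that describes itself as explorative, and the correction is worth making because it is nearly free.

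**What to change.** In Statistical analysis, state the following:
- The T3 minus T0 change in NK phenotype is correlated with the T3 minus T0 change in each metabolic and cardiovascular variable.
- The estimate is made in the trained women, since the objective concerns effects of training. If controls are pooled in, include a group term, so that a difference in mean change between groups is not read as coupling within women.
- The method is a correlation coefficient or linear model suited to continuous changes, with adjustment for confounders such as BMI where planned, in place of the logistic regression for this purpose.
- Associations with baseline levels are a separate question, reported separately with the visit named.

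For the uterine artery indices, Study objectives and design and Study procedures and data collection must first be reconciled on whether a post-intervention measurement exists. Without one, no change can be computed.

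The cost is a sentence or two of wording. The metabolic, tilt-test and maximal oxygen consumption values are already planned at both visits, so no new data are needed.
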